### Data collection

Data will be collected and entered directly by the site personnel into a validated electronic data capture system.

Data collection will include baseline demographics, details of end stage kidney disease and operation details including graft placement, cold ischaemia time and intraoperative fluid volume. In the post-transplant admission period (7 days) data collection will include fluid balance, weight, blood pressure, chest X-ray, oxygen use, red cell transfusion requirement, medication, sodium, dialysis requirement and graft function and survival. Data collection postdischarge but within the first 30 days post-transplant will include date of hospital discharge, details of readmissions and outpatient visits, transplant thrombosis leading to graft failure and graft function, plasma creatinine and height. The economic evaluation data will capture time spent in ward areas of varying acuity, return to theatre, additional investigations and long-term disability. In the event of a patient withdrawal information will be recorded detailing date, who initiated withdrawal and reason.

Data quality will be ensured through specific checks, query management, audit trails and source data verification. Role-based access control and system security measures will be used to protect data integrity and confidentiality. Archiving will be authorised by the Sponsor following submission of the end of study report. Essential documents will be retained for a minimum of 5 years after completion of the trial. Detailed data management procedures are described in the Data Management Plan.

### Statistical plan

#### Sample size

The sample size required is 140 participants randomised. The current mean number of ‘days at home up to 30 days after transplant’ is 16 days, with an SD of 7 days, as obtained from a retrospective analysis of 110 paediatric transplants from 3 centres in 2020–2021. Following review of published data in adult patients, and a consensus reached from the LIMITS patient and public involvement (PPI) group and the Young Persons Advisory Group (YPAG), the study is powered to detect a clinically meaningful difference of 3 days in the number of ‘days at home up to 30 days after transplant’ as this represents an important difference for patients.^14^

Due to the skewed nature of the data, the outcome was log-transformed, and the sample size was calculated on that scale to mirror the final analysis. A two-sided test, with 90% power, 5% type I error, 1:1 allocation, and allowing for two formal interim analyses at 50% and 75% for benefit and harm using non-binding O’Brien-Fleming boundaries, would require 126 participants. After allowing for 10% dropout, for example, if a transplant is unable to proceed following randomisation or the primary outcome cannot be obtained, the total number of participants required is 140.

### Interim analysis

A group sequential design with non-binding O’Brien-Fleming boundaries will inform early stopping of the trial in the case of strong evidence of harm or benefit, while preserving the overall 5% type I error rate. Two interim analyses will be conducted at 50% and 75% recruitment (when 70 and 105 participants have primary outcome data respectively). The independent Data Monitoring Committee (DMC) will review these to inform continuation of the trial alongside their wider review of the safety and integrity of the trial. In addition, the DMC will review serious adverse events (SAEs) at 20% recruitment (28 participants, randomised), in particular delayed transplant function and thrombosis.

### Analysis

The analyses will be described in detail in a full statistical analysis plan. The population used for efficacy analyses will be a modified intention-to-treat analysis which will include all randomised patients who receive a transplant, as although unlikely, it would be illogical to include any participant who did not receive a transplant after being randomised. This will be the primary analysis for the trial, though the primary outcome will also be analysed per protocol, as a sensitivity analysis.

### Primary outcome

The primary outcome, days at home in the first 30 days, will be analysed using a mixed linear regression model. Due to the skewed nature of the data, and to align with the methods used to generate the sample size, prior to the regression model being fitted, a log-transformation will be applied. The model will adjust for donor type (living vs deceased donor) and participant weight (<20 kg and >20 kg pretransplant) as fixed effects, and transplant centre as a random effect.

Sensitivity and subgroup analyses of the primary outcome will be performed using the same model as for the primary outcome, with an additional interaction term for each of the trial arm by subgroup categories. The following subgroup analyses are planned to assess whether the treatment effect differs between these subgroups:

Donor type (living vs deceased donor): It is anticipated that days at home in the first 30 days post-transplant will be fewer for deceased donor kidney recipients.Participant wt (<20 kg and >20 kg pretransplant): It is anticipated that the effect size will be greater for participants <20 kg.

### Secondary outcomes

Secondary outcomes will be analysed using mixed logistic or linear regression models as appropriate with the same risk-adjustment as for the primary outcome. For transplant function at 3 months post-transplant measured by eGFR, transformations will be applied prior to modelling, if appropriate.

Any missing primary and secondary outcome data will be summarised. Primary and secondary outcome measures will not be imputed and these will be treated as missing data and excluded from the relevant analyses. If outcome data are missing for more than 25% of participants, outcomes will not be reported.

To explore if missing values have an undue impact on the primary outcome result, a sensitivity analysis using multiple imputation will be performed if the primary outcome is missing in more than 5% of the participants included in the modified intention-to-treat analysis.

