### Outcome measures

The primary outcome measure for clinical effectiveness is mean days at home in the first 30 days after kidney transplant. The primary outcome measure for cost-effectiveness is kidney related costs within the study period which encompasses all costs incurred and implications for patient health within the study.

Secondary outcome measures are as follows:

Patient-reported experience of transplant hospital stay.Proportion of participants with systemic hypertension (systolic blood pressure above the 95th centile for age and height on 2 consecutive days) within 7 days after transplant.Proportion of participants with pulmonary oedema on chest X-ray within 7 days after transplant.Proportion of participants with severe acute hyponatraemia (defined as plasma sodium concentration <130 mmol/L) within 7 days after transplant.Proportion of participants receiving red blood cells within 7 days after transplant.Proportion of participants with transplant thrombosis in the postoperative period leading to graft failure within the first 30 days.Proportion of participants with delayed transplant function (dialysis within the first 7 days after transplant).Mean transplant function measured by estimated glomerular filtration rate (eGFR) at 3 months post-transplant.^13^

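### The seven-day hypertension model omits the child's pre-transplant systolic pressure, giving up precision on one secondary outcome; the comparison itself stays valid

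*Protocol article*

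**What the plan says.** All references are to the protocol article.

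- **Outcome measures** defines the hypertension outcome as "systolic blood pressure above the 95th centile for age and height on 2 consecutive days", assessed within 7 days after transplant. The definition makes no reference to pressure before transplant. It is one of eight secondary outcomes, introduced only by "Secondary outcome measures are as follows" and not ranked.
- **Secondary outcomes** (statistical plan) prescribes mixed models, logistic or linear according to the outcome, "with the same risk-adjustment as for the primary outcome".
- **Primary outcome** (statistical plan) supplies that adjustment set: "The model will adjust for donor type (living vs deceased donor) and participant weight", split at 20 kg, with transplant centre as a random effect.
- **Data collection** describes the baseline items thus: "Data collection will include baseline demographics, details of end stage kidney disease and operation details including graft placement". Blood pressure is named in the next block: "In the post-transplant admission period (7 days) data collection will include fluid balance, weight, blood pressure".
- **Eligibility criteria** exclude only multiorgan recipients, so children who are hypertensive before transplant can enter. Randomisation is stratified by centre and donor type.

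No pre-transplant prevalence, event rate, effect or power is given for hypertension.

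**The concern.** The Introduction names hypertension among the complications associated with fluid overload, so this outcome bears on the trial's rationale. Its adjustment set was chosen for a different outcome, days at home. The outcome is already standardised for age and height, which probably leaves the 20 kg split little to explain. The covariate one would reach for first, the same child's pressure before transplant, is absent.

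This is more than detail left to the analysis plan: the article fixes the covariates by reference, and an analysis plan that followed it would leave baseline pressure out. At stake are precision and protection against chance imbalance in this one comparison.

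**Working it through.** **Inputs from the article.** 126 evaluable participants, hence 126/2 = 63 per arm, and 126/(1 − 0.10) = 140 randomised. These figures belong to the primary outcome and are taken as given; this point does not depend on how 126 was derived. The plan states no figure for hypertension that could be reproduced.

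**Assumed inputs (not in the documents).** Systolic z-score SD 1.2; event if z > 1.645; event rates of 49% versus 32%, or 30% versus 15%; 49% or 30% of children above the 95th centile beforehand; pre/post correlation ρ of 0.3, 0.5 or 0.7.

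**1. Model.** post = μ + ρ(pre − μ) + noise, less a uniform treatment shift in one arm. For an event rate p the mean is 1.645 − 1.2·z(1−p):
- 49%: 1.645 − 1.2 × 0.025 = 1.615. 32%: 1.645 − 1.2 × 0.468 = 1.083. Shift 0.53.
- 30%: 1.645 − 1.2 × 0.524 = 1.016. 15%: 1.645 − 1.2 × 1.036 = 0.401. Shift about 0.61.

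**2. Closed-form check of unadjusted power** = Φ(difference/SE − 1.96):
- 49% v 32%: SE = √[(0.49×0.51 + 0.32×0.68)/63] = 0.0861; 0.17/0.0861 = 1.97; power about 0.505.
- 30% v 15%: SE = √[(0.30×0.70 + 0.15×0.85)/63] = 0.0732; 0.15/0.0732 = 2.05; power about 0.536.

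**3. Simulated logistic regression, without and with the pre-transplant value.** Two separate sets of runs; ranges cover both pairs of event rates.

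| ρ | Set 1: without | Set 1: with | Set 2: without | Set 2: with |
|---|---|---|---|---|
| 0.3 | 47–51% | 47–51% | 51–54% | 52–55% |
| 0.5 | 47–49% | 52–55% | 50–52% | 57% |
| 0.7 | 49% | 63% | 52% | 65–67% |

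The gain is near zero at ρ = 0.3 and about 14 to 15 points at ρ = 0.7.

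**4. A second model, with baseline status as yes/no.** Assumed conditional odds ratio 0.33, baseline prevalence 30–70%, n = 126. Control-arm event rates are for children hypertensive versus not hypertensive beforehand:
- weak (70% v 50%): power 83.0–83.3% without, 84.0–84.4% with;
- moderate (80% v 40%): 71–75% without, 79–81% with;
- strong (90% v 30%): 44–49% without, 63–65% with.

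The gain runs from about 1 to 22 points, the top needing a very strongly prognostic baseline. With no treatment effect (moderate case, 50% prevalence), rejection rates were 5.1% without and 5.3% with the covariate.

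**5. Chance imbalance.** With an assumed 40% hypertensive beforehand, the between-arm difference in prevalence has SE √(2 × 0.4 × 0.6/63) = 0.087. A gap of 10 points or more has probability 2[1 − Φ(0.10/0.087)] ≈ 0.25, about one trial in four.

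**6. Do children already hypertensive carry information?** Under the model in step 1 their risk difference is the larger one: 0.18–0.20 against 0.14–0.16 in the others (49% v 32%), and 0.19–0.25 against 0.11–0.13 (30% v 15%). Their share of the total effect runs from 0.30 × 0.19/0.15 = 38% to 0.49 × 0.20/0.17 = 58%.

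**Limits.** The simulations score one reading rather than 2 consecutive days. Neither includes centre; the second carries one null binary covariate standing in for donor type.

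**The case against.** The strongest reply is that nothing here is an error. The sections agree with one another, one common adjustment set for all secondary outcomes is conventional, and the test holds its level. Chance imbalance is ordinary sampling variation that the standard error already covers. All of that stands; what remains is an efficiency argument.

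A reader might infer four stronger things, none of which the documents support.

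- *That pre-existing hypertension is wrongly charged to the fluid regimen.* The outcome counts readings after transplant only, and randomisation spreads children already hypertensive evenly across the arms in expectation.
- *That these children dilute the contrast.* Fluid volume can move such a child across the threshold in either direction, and step 6 shows them carrying the larger risk difference under a uniform shift. Dilution appears only if they are assumed to have the same event rate in both arms. For example, at 90% in both, with the others falling from 50% to 25%, a 25-point difference shrinks to 17.5 at 30% prevalence. Nothing in the article supports that assumption.
- *That this is a main outcome.* It is unranked, and the sample size is set for days at home.
- *That baseline pressure goes uncollected.* The Data collection text is a condensed list, its kidney disease details are not itemised, and the supplementary schedule of procedures and the Data Management Plan are not shown.

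**Conclusion.** The point holds as a minor, optional improvement. As written, the hypertension model leaves out a plausible strong predictor, so precision is lost and chance imbalance in baseline pressure is not adjusted for. There is no bias in expectation and no inflation of type I error.

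For correlations of 0.3 to 0.7 the gain from adjusting is roughly 0 to 15 points of power, from an unadjusted level near 50%. It is almost nothing if baseline pressure predicts weakly; the 22-point figure belongs to the extreme of the yes/no model. Every rate, SD and correlation behind these figures is an assumption. That baseline pressure is strongly prognostic is plausible but not documented.

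**What to change.** In Secondary outcomes, and in the analysis plan, state that the hypertension model alone adds the last routine pre-transplant systolic pressure, standardised for age and height, to the common adjustment set. Confirm that this reading is captured at baseline. Prespecify the term before any unblinded comparison, since adding it later would look data-driven.

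The proportion newly hypertensive among children below the 95th centile beforehand may be reported descriptively. It should not replace the outcome, because it would set aside 30% to 49% of the children at the prevalences assumed above, and those children are informative about the treatment effect.

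Cost: one extra baseline field if it is not already there, a few missing baseline values to handle, and an odds ratio that is conditional on baseline pressure and should be labelled so. Treatment, primary outcome and sample size do not change.

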## Introduction

 Kidney transplantation is the treatment of choice for children with end-stage kidney disease. Large volumes of fluid are routinely administered to children following kidney transplant. As a result, complications of fluid overload are frequent.^1^

Excess fluid can cause electrolyte imbalances such as hyponatraemia, which has resulted in reports of cerebral oedema, seizures and even death in severe cases.^2 3^ Fluid overload after transplant is associated with pulmonary oedema, hypertension, delayed wound healing, increased blood transfusions, delayed discharge from hospital.^4 5^ Fluid overload prolongs hospital admission which impacts children’s kidney dialysis and transplant care capacity and increases healthcare costs.^6^

Observational data in paediatric transplant recipients <20 kg and adult kidney transplant recipients have shown favourable outcomes with conservative fluid volume administration.^7 8^ Clinical trial outcomes in adults with sepsis support the non-inferiority of a restrictive fluid strategy compared with previous liberal fluid volumes.^9^ In adult kidney transplant recipients, the traditional practice of large volume fluid administration is no longer recommended^10^ as large fluid volumes do not reduce the proportion of adult grafts that fail or are slow to function as previously thought.^11^

This change in adult transplant practice has not been widely adopted for children despite frequent fluid overload related complications because of a view that the risks and benefits may differ in smaller children.^1^ Central to this is concern about delayed transplant function and/or thrombosis with using a conservative fluid approach. Existing data demonstrate a low risk of transplant thrombosis. One year graft survival in paediatric kidneys is 97% (deceased donor transplant) and 98% (living donor transplant), so the overall risk of graft thrombosis is <3% nationally as vessel thrombosis typically leads to graft loss.^12^

The aim of the LIMITS trial is to determine if relative limitation of fluid volume administered to children receiving kidney transplant is superior to liberal fluid volume administration with a primary outcome of mean days at home up to 30 days after transplant.

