### Cost-effectiveness outcomes

The primary outcome for the cost-effectiveness analysis will be kidney-related costs within the study period. The analysis will be confined to the data observed within the study with all costs incurred and implications for patient health considered.

To supplement the primary economic analyses, a secondary analysis will be conducted that does not assume that efficacy is identical in both arms. This analysis will provide an estimate of the cost for a unit eGFR improvement at 3 months. This will allow clinicians to make judgements on whether any increased costs are justified by the clinical benefit provided.

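### As written, the 3-month mean eGFR is computed in surviving grafts only, because the missing-data rule makes no exception for graft failure or death

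*Protocol article*

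**What the plan says.** The Outcome measures section lists as a secondary outcome "Mean transplant function measured by estimated glomerular filtration rate (eGFR) at 3 months post-transplant". It also lists two other graft outcomes: delayed function, meaning dialysis in the first 7 days, and thrombosis leading to graft failure within 30 days.

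The Secondary outcomes section assigns mixed logistic or linear models. For eGFR it adds only this: "For transplant function at 3 months post-transplant measured by eGFR, transformations will be applied prior to modelling, if appropriate". Its rule for unavailable data is general: "Primary and secondary outcome measures will not be imputed and these will be treated as missing data and excluded from the relevant analyses". Two safeguards follow:

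- Multiple imputation, for the primary outcome only: "a sensitivity analysis using multiple imputation will be performed if the primary outcome is missing in more than 5% of the participants".
- A reporting limit: "If outcome data are missing for more than 25% of participants, outcomes will not be reported".

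The Cost-effectiveness outcomes section uses the 3-month eGFR again in a secondary analysis: "This analysis will provide an estimate of the cost for a unit eGFR improvement at 3 months".

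On the risk to the graft, the Introduction says of the reluctance to change paediatric practice: "Central to this is concern about delayed transplant function and/or thrombosis with using a conservative fluid approach". It adds that vessel thrombosis typically ends in graft loss, and gives one-year graft survival as 97% (deceased donor) and 98% (living donor).

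**The concern.** A child who has died has no eGFR. A child whose graft has failed has no eGFR that describes the graft, since a creatinine taken on dialysis partly reflects dialysis clearance. The article does not say this; it follows from what eGFR measures. Under the exclusion rule these children leave the analysis, and they have the worst graft results.

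This differs from a missed blood test. The article itself names a route by which allocated fluid volume might affect graft loss. Restricting the analysis to surviving grafts then conditions on something that happens after randomisation and may depend on the arm. The comparison is no longer between the randomised groups, and the arm that loses more kidneys gains from it.

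At stake is the only continuous graft-function outcome, and the only one measured at 3 months. It would be read as evidence on whether limiting fluid harms the graft. The economic ratio inherits the problem. When its denominator, the eGFR difference, is near zero, a shift of a couple of units can change the size or sign of the ratio.

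**Working it through.** **The plan's own figures.** The article gives no figure for the eGFR analysis. It gives 126 evaluable children, and 126 / 0.90 = 140 randomised, so the dropout step reproduces. I use 126 / 2 = 63 per arm only as a count.

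**Do the stated safeguards reach this case?** Multiple imputation is tied to the primary outcome, so it does not. The 25% reporting limit would need more than 0.25 × 126 = 31.5 children without eGFR, far above any plausible number of lost grafts.

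**How many children?** The one-year graft survival in the Introduction implies 2–3% loss, used here as an upper guide for 3 months.

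- Of 126: 126 × 0.02 = 2.5 to 126 × 0.03 = 3.8.
- Of 140: 140 × 0.02 = 2.8 to 140 × 0.03 = 4.2.

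That is about 3–4 children in the whole trial. With 70 per arm and equal true risk of 2–3%, binomial probabilities give a chance imbalance of at least 2 losses with probability 0.34–0.44, and of at least 3 with probability 0.12–0.21.

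**How far does the contrast move?** Assumed, because the article gives neither: mean eGFR 60–80 and SD 20–30 mL/min/1.73 m². Let one arm have k more losses than the other, out of 63. Two alternative reference points are used; they do not add.

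- *A: a lost graft counts as 0.* The hidden difference is mean × k/63. For k = 2: 60 × 2/63 = 1.9 to 80 × 2/63 = 2.5.
- *B: the lost kidneys would have been the k lowest values of a normal distribution.* The upward shift is SD × φ(z_p)/(1 − p), with p = k/63. For k = 2 the multiplier is 0.0736, giving 20 × 0.0736 = 1.5 to 30 × 0.0736 = 2.2. For k = 4 it is 0.133, giving 2.7 to 4.0.

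The standard error of the difference between arms is SD × √(2/63): 20 × 0.178 = 3.6 to 30 × 0.178 = 5.3.

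| Excess losses k | A: scored 0 | B: lowest values removed | Combined range |
|---|---|---|---|
| 2 | 1.9–2.5 | 1.5–2.2 | 1.5–2.5 |
| 4 | 3.8–5.1 | 2.7–4.0 | 2.7–5.1 |

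For k = 2 the shift is below one standard error throughout: the largest ratio is 2.54/3.56 = 0.71. For k = 4 it runs from 3.81/5.35 = 0.71 to 5.08/3.56 = 1.43 standard errors.

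**Which losses are seen elsewhere?**

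| Event | Listed outcome that counts it |
|---|---|
| Dialysis in the first 7 days | Delayed transplant function |
| Thrombotic graft failure to day 30 | Transplant thrombosis |
| Non-thrombotic graft failure after day 7 | None |
| Any graft failure from day 30 to month 3 | None |

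Non-thrombotic failure in the first week is caught only if it leads to dialysis then, and is recorded as delayed function rather than as loss. Deaths are reported as serious adverse events but are not tied to the eGFR analysis.

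**The case against.** The strongest case is that a separate statistical analysis plan is announced, and that the handling of graft failure in one secondary outcome belongs there. That would settle the matter if the article were silent. It is not: it fixes exclusion, without exception, for all secondary outcomes. An analysis plan that scored lost grafts would depart from that sentence, so the sentence itself needs changing.

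A second objection is that the article never says a failed graft counts as missing, and a site might enter a creatinine taken on dialysis. This is fair. The exclusion of these children is an inference. But the alternative leaves a number that does not measure the graft, so a rule is needed either way.

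A third objection concerns size, and it stands. Few children are affected, and the likely shift is below one standard error. Putting all expected losses in one arm would be an extreme case.

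A reader might infer that graft harm would go unseen altogether. The documents do not support that: delayed function and thrombotic graft failure are compared by arm, and the data monitoring committee reviews both. Nor do they predict more losses with conservative fluids. They report that clinicians fear this, and cite adult evidence that large volumes do not reduce the proportion of grafts that fail or are slow to function.

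**Conclusion.** The point holds for the 3-month eGFR outcome and for the cost per unit of eGFR that uses it. As written, the rule yields a mean among surviving grafts, biased upward in the arm with more losses, and no stated sensitivity analysis would show it. The primary outcome and the sample size are not affected.

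The expected size is modest: about 3–4 children, and a shift of about 1.5–2.5 mL/min/1.73 m² for an excess of 2 losses. It becomes comparable with the standard error only with an excess of about 4, which is roughly all the losses expected in the trial. The direction does not depend on the assumed eGFR mean and SD; the size does. It also rests on the inference that a failed graft yields no usable eGFR.

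It would go too far to conclude that mean eGFR must be abandoned for a rank analysis. The mean in functioning grafts is a legitimate summary if it is labelled as such and accompanied by an analysis that counts the losses. The change is worth making because it is cheap and because these losses are only partly covered elsewhere.

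**What to change.** 1. In Secondary outcomes, state that graft failure or death before 3 months is an outcome and not missing data. Limit the exclusion rule to eGFR that is truly missing, such as a child with a working graft and no blood result.
2. Pre-specify, before anyone sees data by arm, an eGFR analysis that gives these children a fixed worst value or worst rank, with the planned adjustment. Place it beside mean eGFR in functioning grafts, labelled as conditional on graft survival. If eGFR may be log-transformed, the fixed value must be usable on that scale; zero is not.
3. Report graft loss from any cause, and death, to 3 months by arm.
4. In Cost-effectiveness outcomes, use the fixed-value version at least as a sensitivity analysis. Ranks will not serve there, because they carry no eGFR unit.

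The cost is a few sentences and one extra analysis. The new result will depend on the value assigned. A graft-status item at 3 months may have to be added: the Data collection section names graft survival only for the 7-day admission period, with thrombotic graft failure and graft function listed to day 30.

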### Treatment

Participants randomised to the intervention arm will receive usual fluids with the volume administered capped to a maximum rate of 150 mL/m^2^/hour for no longer than 18 hours following transplant, then reduced to a fixed daily fluid target not exceeding 1.5 L/m^2^/day thereafter until day 5. No specific urine output is targeted. Diuretics should not be administered intraoperatively nor postoperatively.

Patients randomised to the comparator arm will receive usual fluids to replace urine output plus insensible losses for at least 48 hours following transplant. Target urine output will be >2 mL/kg/hour and diuretics can be given as per the clinical team’s usual practice.

The choice of intravenous fluid (control or intervention) and decision to discontinue intravenous fluid and switch to enteral fluid will be determined by the treating clinician. All participants will receive routine clinical transplant care with no additional investigations or outpatient visits (figure 1, see onlinesupplemental files 1^4^ for schedule of procedures).

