### Patient Reported Experience Measures: Hospital Stay Experience Questionnaire

A patient-reported experience questionnaire has been developed for this trial to better understand the patient and family experience of their transplant hospital admission. On the day of discharge the relevant version of the Hospital Stay Experience Questionnaire (HSEQ) will be completed anonymously by both the participants and their parent(s)/carer(s). Younger children or those with a learning disability may receive assistance with completion from their parent(s)/carer(s). For children under the age of 7, a parent/carer HSEQ only will be completed.

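### The rule that outcomes with more than 25% missing data go unreported would withhold prespecified results on a data-dependent trigger, and sits badly with the imputation plan beside it

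*Protocol article*

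**What the plan says.** The provisions on missing outcome data stand together in the Protocol article under Secondary outcomes:

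- Description: "Any missing primary and secondary outcome data will be summarised".
- Main handling: "Primary and secondary outcome measures will not be imputed and these will be treated as missing data and excluded from the relevant analyses".
- Non-reporting: "If outcome data are missing for more than 25% of participants, outcomes will not be reported".
- Sensitivity analysis, for the primary outcome only: "a sensitivity analysis using multiple imputation will be performed if the primary outcome is missing in more than 5% of the participants" in the modified intention-to-treat set.

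The section heading might suggest that the non-reporting rule concerns secondary outcomes alone. But the sentence just before it covers both kinds, and the rule carries no exemption. No missing-data sensitivity analysis is stated for secondary outcomes.

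**The concern.** Whether a prespecified outcome appears in the results should not depend on the data. Under this rule it does: once missingness passes a fixed fraction, the outcome is not shown at all, not even with a warning. Readers would lose the estimate and its uncertainty, and a later meta-analysis would lose the trial for that outcome. If missingness is related to arm or to prognosis, which is possible in an open-label trial, the withheld results are not a random subset.

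The rule also pulls against its neighbour. Multiple imputation is planned because missing values might distort the primary result. That worry grows with the amount missing, yet above 25% the result that the imputation was meant to test is itself withheld.

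This is stated text, not a detail left for later. A statistical analysis plan could undo it only by departing from the published protocol.

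**Working it through.** **Inputs (Protocol article).** Sample size: 140 randomised, 126 evaluable, 10% dropout. Secondary outcomes: thresholds of 25% and 5%. Introduction: one-year graft survival of 97% (deceased donor) and 98% (living donor).

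**1. The plan's own figure.** 126 / (1 − 0.10) = 140, which reproduces. The plan therefore expects about 140 − 126 = 14 children without primary outcome data. Some of these would be transplants that did not proceed, and they fall outside the modified intention-to-treat set.

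**2. Where the thresholds lie.** Both rules say more than, so the count must exceed the fraction.

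- 25% of 140 = 35, so the rule acts from 36 missing. 25% of 126 = 31.5, so it acts from 32.
- 5% of 140 = 7, so imputation starts at 8 missing. 5% of 126 = 6.3, so it starts at 7.

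On 140 children, the primary outcome is reported with an imputation analysis from 8 to 35 missing, and is not reported from 36 upwards.

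**3. Chance of crossing the 25% line.** Let X be the number missing for one outcome, X ~ Binomial(N, p), with missingness independent between children. The rule acts with probability P(X ≥ 36) for N = 140, or P(X ≥ 32) for N = 126.

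| True missingness p | N = 140 | N = 126 |
|---|---|---|
| 10% (planned dropout) | about 0 | about 0 |
| 15% | 0.0007 | 0.0016 |
| 20% | 0.06 | 0.08 |
| 25% | 0.45 | 0.49 |
| 30% | 0.89 | 0.89 |

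Only the 10% row rests on a rate in the document. The others are assumed values, to show where the rule starts to act: at about 20% or more.

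**4. Can graft loss trigger the rule?** Taking one-year loss of 2% to 3% as an upper bound for loss by 3 months, 140 × 0.02 = 2.8 and 140 × 0.03 = 4.2, so about 3 to 4 children are expected at most. That is far below 36.

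**The case against.** The best defence is that the rule is remote where the document gives a rate, that missing data will be summarised in any case, and that declining to publish an estimate based on under three quarters of participants is cautious. The first two points stand and limit the size of the problem. The third does not: an unreliable estimate can be reported as unreliable, and a summary of how much is missing does not replace the result.

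A reader might infer more from the complete-case sentence. Three stronger readings are tempting, and the document supports none of them as fact.

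- **Pulmonary oedema would be compared only among children who had a chest X-ray.** Care is routine ("All participants will receive routine clinical transplant care with no additional investigations or outpatient visits"), so X-rays may not be universal. But Outcome measures defines this outcome as a proportion of participants, and nothing codes a child without an X-ray as missing.
- **The questionnaire would be suppressed if more than a quarter are under 7.** The article says "For children under the age of 7, a parent/carer HSEQ only will be completed". For those children the parent/carer form is the relevant version, so a child form that was never due is not applicable, not missing.
- **Failed grafts would drop out of the eGFR comparison and hide harm.** The outcome is "Mean transplant function measured by estimated glomerular filtration rate (eGFR) at 3 months post-transplant", and the article neither gives failed grafts a value nor calls them missing. A full analysis plan may settle this. A split of 3 against 1 losses with 63 per arm and a mean eGFR of 70 would shift the difference by (3/63 − 1/63) × 70 = 2.2 units, but both the split and the mean are assumed. An even split gives zero. Harm is also tracked separately, by delayed transplant function and by "Proportion of participants with transplant thrombosis in the postoperative period leading to graft failure within the first 30 days", although later or non-thrombotic loss has no outcome of its own.

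**Conclusion.** The non-reporting rule is a defect as written and should be changed. It applies to primary and secondary outcomes, acts from 36 missing of 140, and is inconsistent in spirit with imputing the primary outcome above 5% missing.

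Its practical reach is limited. At the planned 10% dropout it will almost certainly not touch the primary outcome. It becomes a real risk for any outcome with about 20% or more missing, and the plausible candidates are secondary outcomes that rely on routine care or on questionnaires. The document gives no missingness rate for these, so how likely any one of them is to be withheld cannot be stated. The probabilities assume independent missingness and that the rule is applied outcome by outcome, which the sentence does not spell out.

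The finding does not extend to how children without an X-ray, children under 7 or failed grafts are coded. The document is silent or points the other way, so these are matters to clarify, not errors.

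**What to change.** Delete the 25% rule. State instead that every prespecified outcome will be reported, with numbers analysed and missing by arm. Where missingness is high, give the estimate with a caveat and add a missing-data sensitivity analysis, for example multiple imputation, for secondary outcomes as well as the primary.

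Two sentences of clarification would forestall the readings above:

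- Pulmonary oedema keeps all modified intention-to-treat participants as its denominator, as its definition already implies.
- The 3-month eGFR analysis has a supportive analysis that accounts for graft loss or death.

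The cost is protocol and analysis-plan wording and modest extra analysis. The sample size stays at 140. The price is that some outcomes will appear with wide, heavily qualified estimates. The change is best made before the first interim analysis, due when 70 participants have primary outcome data, so that it cannot be seen as a response to results.
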